## Abstract

**Introduction::**

Blunt chest trauma (BCT) accounts for up to 65% of polytrauma patients. In patients with 0 to 2 rib fractures, treatment interventions are typically limited to oral analgesics and breathing exercises. Patients suffering from BCT experience symptoms of severe pain, poor sleep, and inability to perform simple daily life activities for an extended period of time thereafter. In this trial, we aim to investigate the efficacy of acupuncture as a functional and reliable treatment option for blunt chest trauma patients.

**Methods::**

The study is designed as a double-blind randomized control trial. We will include 72 patients divided into 2 groups; the acupuncture group (Acu) and placebo group (Con). The acupuncture group will receive true acupuncture using a uniquely designed press tack needle. The control group will receive placebo acupuncture treatment through the use of a similarly designed press tack needle without the needle element. The acupoints selected for both groups are GB 34, GB 36, LI 4, LU 7, ST 36, and TH 5. Both groups will receive 1 treatment only following the initial visit to the medical facility and upon diagnosis of BCT. Patient outcome measurements include: Numerical Rating Scale, Face Rating Scale, respiratory function flowmeter, Verran Snyder-Halpern sleep scale, and the total amount of allopathic medication used. Follow-up time will be scheduled at 4 days, 2 weeks, and lastly 3 months.

**Expected outcome::**

The results of this study can potentially provide a simple and cost-effective analgesic solution to blunt chest trauma patients. This novel study design can serve as supporting evidence for future double-blind studies within the field of acupuncture.

**Other information::**

The study will be conducted in the thoracic surgical department and acupuncture department in China Medical University Hospital, Taichung, Taiwan. The study will be conducted on blunt chest trauma patients and is anticipated to have minimum risk of adverse events. Enrollment of the patients and data collection will start from March 2020. Study completion time is expected in March 2022.

**Protocol Registration::**

(CMUH109-REC1-002), (NCT04318496).

## Introduction

1

The rib cage and associated anatomical structures are responsible for protecting the vital organs located within the chest cavity.^[1]^ The occurrence of blunt chest trauma (BCT) typically involves multiple levels of injury including heart rupture, aortic dissection, lung contusion, rib fracture, or simple soft tissue injury. In the case of preserved organ function, it is the bony structures and soft tissues which are most commonly affected by BCT injury.^[1]^ According to previous literature, BCT patients can be divided into 3 levels based on the severity of injury as identified by chest plain film findings. Level 1 includes patients without rib fractures; level 2 includes patients with 1 or 2 rib fractures; and level 3 includes patients with more than 2 rib fractures.^[2]^ Based on retrospective studies, level 3 patients experience increased frequency of hospitalization, thoracotomies, and a higher mortality rate. Levels 1 and 2 patients are commonly treated as out-patients, but still suffer greatly from chest pain and tend to experience breathing difficulties.^[2,3]^ The pain associated with the BCT injury may in turn lead to the inability have sufficient sleep, with the resultant lack of rest impeding the recovery process.^[4]^ The most commonly used conventional treatments are analgesics.^[1,5]^ Moreover, while nerve block surgical intervention is also practiced as a treatment intervention, it is commonly reserved for level 3 patients experiencing severe pain and/or thoracic deformity.^[1,5]^ While analgesic medication can relieve pain temporarily, most patients still suffer prolonged nociceptive hypersensitivity and usually have difficulties in performing daily life activities for sometime after. Furthermore, elderly and renal insufficiency patients are at a higher risk of experiencing harmful effects from long term use of analgesics and muscle relaxants.^[6]^

For thousands of years, acupuncture has been used in the treatment of all kinds of traumatic injuries. Moreover, in recent decades, stimulation of acupuncture points for the treatment of visceral pain, post-operative pain, cancer pain, and chronic pain is well established and has been widely investigated in a number of clinical trials.^[7–9]^ Accordingly, in order to maintain an unbiased approach, the acupuncture intervention of this particular study will be compared to a placebo intervention. Our study implements a novel design that maintains clinical efficacy, through the use of press tack needles and similar placebos that look identical, hereby ensuring blindness of both the patient and the acupuncturist.^[10]^

With a goal to improve the analgesic effect and life quality in patients suffering from BCT, we designed a double-blind study comparing press tack acupuncture to press tack placebo interventions. In the trial, we aim to investigate the efficacy of press tack acupuncture based on traditional acupuncture concepts and point locations. Furthermore, we hypothesize that press tack acupuncture will have a superior analgesic effect when compared to press tack placebos.

## Methods

2

### Design and setting

2.1

The study is designed as a single-center randomized control, parallel-arm, double-blinded trial. It will take place in the out-patient clinic of China Medical University Hospital. The study will be conducted from March 2020 to March 2022. The study was approved by the institutional review board of China Medical University Hospital (CMUH109-REC1-002), and was registered on clinicaltirl.gov (NCT04318496).

The main goal of the study is to reduce pain and improve the respiratory function and sleep quality of patients after BCT. The participants will be divided to 2 groups; acupuncture group (Acu) who will receive the true press tack needles, and a placebo group (Con) who will receive press tack placebos on the same acupoints without the needle element. Patient outcome measurements include: Numerical Rating Scale (NRS), Face Rating Scale (FRS), respiratory function flowmeter Verran Snyder-Halpern sleep scale (VSH), and the total amount of allopathic medication used.

### Participants

2.2

We will include a total of 72 patients who are suffering from BCT. After the patient's accident, such as falls, kicks, fights, or traffic accidents, they will be sent to the emergency room and visit a chest surgical out-patient clinic for treatment and follow-up. Those who meet the inclusion criteria will be informed about the study and can freely choose to participate. They will sign the informed consent and will be randomized accordingly, with commencement of the study occurring immediately. The patients are allowed to drop out from the study at any time point of the study.

### Inclusion criteria

2.3

Age 20 to 80 years old.Patients who have chest trauma as described by themselves or based on medical chart records within 1 week of injury.Injury Severity Score (ISS) is less than 18 points.Body mass index < 30.

### Exclusion criteria

2.4

Sternal fracture.ISS is equal to or more than 18 points.History of intercostal nerve injury.History of cardiovascular disease.History of chronic lung disease.Significant lung mass or chest deformity noted in the chest plain film.

### Informed consent

2.5

From the informed consent discussion and form, the intervention, risks, benefits, and patient's rights in the study will be explained in a simple language that patients can clearly understand (by an hospital doctor). The informed consent will be signed by the patient or by a legal guardian. In the circumstance that they wish to withdraw from the study, our strategy is to use the available data for the final analyses and accommodate the patients’ wishes accordingly.

### Randomization and allocation concealment

2.6

The participants will be randomized into 2 groups with a 1:1 ratio produced by the SPSS program software, version 22. A computer-based simple random sampling with a 1:1 ratio without stratification will be used. A number (1–72) will be affiliated to each patient at the time of their first visit to the out-patient clinic and after completing the informed consent. The number, patient name, and date of birth will be written down on a non-transparent envelope by a study nurse 1 (researcher [name]). Inside the envelopes, there will be 14 separate sterile press tack needles or identical looking press tack placebos. The envelopes in both groups will appear identical. Study nurse 1 will write down the number, patient name, and intervention in an electronic chart and create a file for each patient.

### Blinding

2.7

Study nurse 1 will be responsible for randomization and prepare the needles in the envelopes. Outside the envelopes, there will be a number belonging to 1 patient, and inside the envelopes, there will 14 separate sterile needles which can be either true press tack needles or press tack placebos. The envelopes and the pouch of needles will look the same. The acupuncturist will be asked not to check the needles when they insert them. At the time of acupuncture, a nurse will accompany the acupuncturist and will verify that he/she is not examining the needles closely. Study nurse 2 will perform the outcome measurement tests. The acupuncturist, patients, and study nurse 2 will be blinded to patient allocation.

### Procedure/interventions

2.8

The participants will be divided into 2 groups. One group will receive press tack needle acupuncture (Acu); the other group will receive press tack needle placebos without the needle element (Con). Both groups will receive 2 individual treatments on the same set of acupoints. The needle retention time will be 4 days. Needle withdrawal will be done by the acupuncturist or acupuncture nurses who have trained in needle withdrawal techniques in the out-patient clinic (Fig. 1).

**Figure 1 F1:**
[figure not shown]
The figure describes the trial processes at a descending order.

### Press tack needle introduction

2.9

In the protocol, the press tack needles (PYONEX*Φ*0.20 mm × 0.6 mm made by Seirin Corporation) have a diameter of 0.2 mm and a length of 0.6 mm. Each needle is packed separately in a sterilized pouch. As for the placebo, the individual press tack and pack are identical to the press needles, except the needle element has been removed. Both interventions will be performed by a qualified acupuncturist and a medical doctor with at least 1 year of experience in acupuncture practice.

### Acupuncture group (Acu)

2.10

The patient will lay down in a supine position on the treatment bed and allowed an adaptive relaxation period of 5 minutes. The acupuncturist will start to sterilize the specific body surface areas over the acupoints with a 70% alcohol pad. Accordingly, the bilateral acupoints of GB 36 (Waiqiu), GB 34 (YangLingQuan), ST 36 (Zusanli), LI 4 (HeGu), LU 7 (LieQue), TH 5 (Waiguan) were chosen for both groups. Each patient will receive 12 press tack needles in total. The needle's depth of insertion will be 0.6 mm. The acupuncturist will manually press the press tack needles over the above-mentioned acupoints without any needle manipulation or “De Qi” sensation. The participants will lay on the treatment bed for the duration of 30 minutes. After the aforementioned process, the vital signs, pain levels, and flowmeter will be recorded again to represent the immediate effect after acupuncture. Finally, the acupuncturist will educate the patients about the total number of press needles and the allotted time of retention. The press tack needle retention time will total 4 consecutive days.

### Placebo group (Con)

2.11

The participants in the placebo group will experience the same treatment course including the selection of acupoints and associated outcome measurement recording. However, the placebo group participants will receive press tack placebos (Pyonex; Seirin Corporation, Shizuoka, Japan). The press tack stickers on the skin surface are identical but without any needle penetrating the skin. The placebo sticker retention time will be the same as in the acupuncture group, totaling 4 consecutive days (Figs. 2 and 3).

**Figure 2 F2:**
[figure not shown]
(A) Press tack needles have an adhesive surface with a needle diameter of 0.2 mm and a length of 0.6 mm. Press tack placebos have an identical adhesive surface without a needle (Pyonex; Seirin Corporation, Shizuoka, Japan). (B) The outer surface of both press tack needles and press tack placebos looks identical.

**Figure 3 F3:**
[figure not shown]
Acupoints used in the trial for both groups: GB 36 (Waiqiu), GB 34 (YangLingQuan), ST 36 (Zusanli), LI 4 (HeGu), LU 7 (LieQue), TH 5 (Waiguan).

### Drug treatment

2.12

Both groups of participates will also receive the prescribed analgeasic medication and/or muscle relaxants. The frequency of the prescribed medicine is 3 to 4 times a day along with meals and before sleep for 7 days. The purpose of the medication is for pain relief, therefore, the participants can discontinue the medication at will.

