### Outcome measures

2.13

The main outcome measurement will be the pain levels of both rest and mobile status for the BCT patients (the mobile status includes cough, deep breath, and turn over on the bed). The patient will measure their pain according to 3 subjective pain scales, namely the NRS, and FRS before treatment, 30 minutes after treatment and 4 days after the press tack needles/placebo intervention. Furthermore, a follow-up will assess the NRS pain scale telephonically at 14 days and 3 months after the initial intervention.

Secondary outcome measurements will include the improvement of respiratory function, sleep quality, and amount of medication used (specifically analgesics and muscle relaxants). We used the portable triflow flowmeter and VSH sleep scale as objective tools for the aforementioned purposes. The patients will be educated on the use of the flowmeter by the affiliated thoracic surgeon. Patients will be allowed as much time as needed to practice the use of the flowmeter before the first measurement is taken. When the patient is ready, the study personnel will commence the measurements of 3 attempts, and will record the best 2 attempts. The triflow flowmeter measures the amount of air the patient can exhale; it has 3 chambers with their own balls that require air pressures from 600 to 1200 cm^3^ per second to elevate. 1200 cm^3^ is the highest score and indicates good exhalation power. The above process will be done before intervention, 30 minutes after intervention and 4 days after the intervention. The patient will also answer the VSH sleep scale in Mandarin to evaluate the sleep quality of the night before the clinic visit. They will complete the questionnaires accordingly at every clinic visit, for a total of 2 times (on day 1 and day 4). Finally, on the 4th day after the initial intervention, participants will bring back the prescribed medication, including analgesics and/or muscle relaxants that were left unused, to be measured for the amount of medication used.

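### The amount of medication used by day 4 reflects what was prescribed as well as what was needed, and the plan neither adjusts for the prescription nor fixes it before allocation

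*Protocol article*

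**What the plan says.** **Prescribing (Protocol article, 2.12 Drug treatment).** "Both groups of participates will also receive the prescribed analgeasic medication and/or muscle relaxants". On how often and how long, this section then adds: "The frequency of the prescribed medicine is 3 to 4 times a day along with meals and before sleep for 7 days". Patients may stop: "therefore, the participants can discontinue the medication at will". Intake above the prescription is not described.

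**Outcome (2.13 Outcome measures).** The secondary outcomes include the "amount of medication used (specifically analgesics and muscle relaxants"). On day 4, "participants will bring back the prescribed medication, including analgesics and/or muscle relaxants that were left unused, to be measured for the amount of medication used". The abstract calls the outcome "the total amount of allopathic medication used".

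**Analysis (2.19 Statistical analysis).** The section lists t tests, chi-squared tests, one-way ANOVA for pain and sleep, a repeated-measures analysis and rank tests for small samples. It names no test specifically for medication use and no covariate for any comparison. Medication use also appears there as a subgroup factor.

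**Blinding and order of steps.** Section 2.7 states: "The acupuncturist, patients, and study nurse 2 will be blinded to patient allocation". The prescriber is not named. Section 2.2 has randomisation follow consent, with the study starting at once. No section says whether the prescription comes before or after allocation.

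**The concern.** The amount used is the amount dispensed minus the amount returned. Two patients with the same pain and the same willingness to take tablets will record different amounts if one was given a single drug class three times a day and the other two classes four times a day. The outcome then mixes a clinic decision with the patient's need.

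Two things could be at stake. The first is precision: variation in prescribing that has nothing to do with the needle widens the spread of the outcome and can hide a real drug-sparing effect. The second is conditional. If prescribing came after allocation and the prescriber learned the arm, a difference in prescribing could pass for a treatment effect. Because the order of the two steps is left open, the article does not exclude the second possibility, but it does not show it either.

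**Working it through.** The article gives no figure for this outcome. Its sample size (2.16) concerns pain and is not involved here.

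**Inputs from 2.12 and 2.13:** one or two drug classes; 3 or 4 times a day; 7-day supply; return on day 4. **Assumption:** one unit per class per dosing time.

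**1. Spread due to prescribing alone** (classes × times a day × days)

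| Regimen | Use as prescribed to day 4 | 7-day supply | Left on day 4 if all taken |
|---|---|---|---|
| 1 class, 3 times | 1×3×4 = 12 | 21 | 9 |
| 1 class, 4 times | 1×4×4 = 16 | 28 | 12 |
| 2 classes, 3 times | 2×3×4 = 24 | 42 | 18 |
| 2 classes, 4 times | 2×4×4 = 32 | 56 | 24 |

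The ratio of largest to smallest is 32/12 = 2.67. A patient who takes half of the largest regimen uses 16 units, more than a patient who takes all of the smallest (12). The total does not rank these two by the share of their prescription that they took.

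**2. Cost in precision.** Let *p* be the units prescribed to day 4. Let the share taken have mean *m* and SD *s*, independent of *p*. Then

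- Var(used) = E[p²](m² + s²) − (m·E[p])²
- residual variance given *p* = E[p²]·s²
- sample-size factor = Var(used) / residual variance

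Assume the four regimens are equally common, m = 0.6 and s = 0.25.

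- E[p] = (12+16+24+32)/4 = 21
- E[p²] = (144+256+576+1024)/4 = 500
- Var(used) = 500 × 0.4225 − 12.6² = 211.25 − 158.76 = 52.5, so SD 7.2
- Residual = 500 × 0.0625 = 31.25
- Share of variance due to prescription = 1 − 31.25/52.5 = 0.40
- Factor = 52.5/31.25 = 1.68

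Over four regimen mixes and three uptake assumptions the factor ran from 1.44 to 2.84. These are not bounds.

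- If every patient had one class and only frequency varied (12 or 16 units, equally common, same uptake), then E[p] = 14, E[p²] = 200, Var(used) = 200 × 0.4225 − 8.4² = 13.94 and residual = 12.5. The factor is only 1.12.
- If uptake were higher and more uniform (m = 0.8, s = 0.15, four regimens equally common), Var(used) = 500 × 0.6625 − 16.8² = 49.01 and residual = 11.25. The factor is 4.4.

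**3. Chance imbalance.** Randomisation is unstratified with 36 per arm. If half of the patients receive two classes (assumed), the 95% limit for a chance difference between arms is 1.96 × √(0.5 × 0.5 × 2/36) = 0.23, or 23 percentage points. A baseline covariate corrects for this too.

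**4. Blinded roles against order of steps.** Section 2.7 lists three blinded parties, and the prescriber is not among them. Sections 2.6 and 2.7 give knowledge of allocation only to study nurse 1, who also enters the intervention in an electronic chart. Who can open that entry is not stated. The two sections together leave the prescriber's status undetermined.

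**The case against.** **Silence in a condensed article.** The Statistical analysis section names no test for medication use, and units, scaling and covariates may be set in a document that is not shown. This stands in part: a missing covariate would be weak as a finding by itself. But the article does fix a total amount, obtained from returns, under prescribing that may vary. A later analysis plan also cannot restore the order of prescribing and allocation, or the prescriber's blinding, once patients have been treated.

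**Only precision is lost.** With a prescriber who does not know the arm, randomisation balances prescribing on average and the unadjusted comparison is valid. This stands in full.

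**The sizes are assumed.** This also stands. The stated frequency may describe one regimen with an optional bedtime dose instead of a difference between patients. Patients in more pain may be prescribed more, so the prescription may itself carry some information on need. The article gives neither the regimen mix nor the uptake.

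**Stronger readings that the document does not support.**

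- *Prescribing is biased by arm.* A reader might infer this from the list in 2.7. Absence from that list is not evidence of knowing the arm, and the envelopes and devices are described as looking alike. An illustration with two classes given to 60% of one arm and 40% of the other yields 0.2 × 14 × 0.6 = 1.7 units, where 14 is 3.5 doses a day over 4 days, or 1.7/7.2 = 0.23 SD. That assumes the very imbalance that would have to be shown.
- *The outcome is the number of units left over.* Section 2.13 has the leftovers measured in order to obtain the amount used.
- *Use cannot exceed 12 to 32 units by day 4.* Those figures are use as prescribed. The supply in hand is 21 to 56 units.

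**Conclusion.** The point holds as one of precision and of an unsettled procedure. The amount used depends on the prescription as well as on need. As-prescribed use to day 4 varies 2.67-fold if one unit is counted per class per dosing time and if both the number of classes and the frequency differ between patients. The comparisons that the article lists take no account of this.

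If the prescriber does not know the arm, the consequence is avoidable noise. Its size cannot be read from the document: roughly 1.4 to 2.8 times the sample for this outcome over the mixes examined, close to nothing if nearly all patients get the same regimen, and more if uptake is high and uniform. Bias would need a prescriber who knows the arm, which the document leaves open and does not show.

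Only a secondary outcome is affected. The sample size and the comparison of pain do not depend on it.

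**What to change.** 1. **Order and blinding (2.7, 2.12).** State that the prescription is completed before the study number is assigned, and add the prescriber to the blinded roles. Choice of drug and dose remains with the clinic.
2. **Record.** Note the amount prescribed per drug class, and the unit, when the prescription is written.
3. **Analysis (2.19).** Compare the total amount used by randomised arm, with the prescribed amount per drug class as a pre-randomisation covariate.

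Two cautions apply. Keep the total as the outcome: dividing by the prescription would answer a different question, since full use of one class and full use of two would both count as 100%. And do not adjust for prescriptions written after allocation: they may be influenced by the arm, and adjusting for them could remove part of a real effect or introduce bias.

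The cost is about three sentences. No new data are needed, because computing use from returns already requires the dispensed count. The downside is that the order of two steps at the first visit becomes fixed.
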